#### Statistical and Qualitative Analysis

Our expectation for the primary outcome is the reduction and stabilization of blood pressure. For the secondary outcome, we hope for acceptance of the eHealth platform and improvements in treatment adherence, physical activities, and dietary intake. A priori levels will be set according to the assessment tool and the expected outcome. The acceptance of the eHealth platform will consider good scores obtained in the analysis of usage logs and questionnaires of engagement, SUS, and TAM. Improved adherence to treatment will consider MBG questionnaire scores measured before and after the intervention. For the analysis of physical activities and dietary intake, a binary outcome will consider whether the patient has adequate levels, diagnosed according to the SISVAN’s questionnaire and standards.

For qualitative data, we will use Minayo’s guidelines [30]. Numeric data will be analyzed with statistical software SPSS 22 (IBM Corp, Armonk, New York). We will calculate the measures of central tendency and dispersion of the quantitative variables, and we will use the Kolmogorov-Smirnov test to verify normality. Basic quantitative data will be determined by mean, standard deviation, and median. Categorical data will be determined by simple frequency. Blood pressure data will be analyzed with the paired *t* test. Either the paired *t* test (parametric) or the Wilcoxon test (nonparametric) may be applied to compare other quantitative variables before and after the intervention. To assess treatment adherence, physical activity, and dietary intake after intervention, we will apply the Chi-square test while considering the app use as the dependent variable; the independent variables will be treatment adherence, physical activity, and dietary intake. For the MBG questionnaire, we will apply the Mann-Whitney test to compare the score between the groups before and after the intervention. The same test may be used to compare diastolic and systolic blood pressure measurements between the preintervention and postintervention groups. We will consider a 95% confidence interval (*P*<.05).

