To evaluate the findings’ heterogeneity (primary and secondary outcomes), we will apply a statistical technique to verify whether the differences observed in the results can be explained by chance. We will apply the Chi-square test with a significance level of *P*<.10. The magnitude of heterogeneity will be assessed by calculating the I^2^ value, which ranges from 0% to 100%. An I^2^ greater than 50% indicates substantial heterogeneity, and an I^2^ above 75% indicates considerable heterogeneity. For the evaluation of heterogeneity, we will consider the demographic and socioeconomic variables. In the presence of heterogeneity, we will investigate its causes through sensitivity analysis. In the sensitivity analysis, the form of data analysis varies, to identify the impact of this change on the results. All analysis techniques can be adjusted or modified, if required, by the characteristics of the collected data. If feasible, we also intend to analyze the results with logistic regression of preintervention and postintervention data. In this case, the dependent variable will consider the base category *whether* [user] *used the app*, related to independent, categorized, and continuous variables of interest such as sociodemographic variables and the expected secondary outcomes.

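### Heterogeneity across demographic strata of one 68-patient trial is graded by I-squared bands that have no calibrated meaning there, and a flag leads to unnamed changes of analysis

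*Protocol article*

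**What the plan says.** All of this is in the protocol article, under Statistical and Qualitative Analysis.

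- Scope: "To evaluate the findings’ heterogeneity (primary and secondary outcomes"), so every outcome is covered.
- Test: "We will apply the Chi-square test with a significance level of *P*<.10". The other tests use the conventional 5% level ("We will consider a 95% confidence interval").
- Size: "The magnitude of heterogeneity will be assessed by calculating the" I-squared value, where a value "greater than 50% indicates substantial heterogeneity" and one "above 75% indicates considerable heterogeneity".
- Strata: "For the evaluation of heterogeneity, we will consider the demographic and socioeconomic variables". Neither the variables nor their number is given here.
- Consequence: if heterogeneity is present, its causes are pursued by sensitivity analysis, described as follows: "In the sensitivity analysis, the form of data analysis varies, to identify the impact of this change on the results". No alternative form is named.

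The same section plans paired t tests for blood pressure, with Mann-Whitney as a possibility. It states no between-group model that gives an effect estimate and standard error within a stratum.

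**The concern.** The I-squared bands come from meta-analysis, where many study estimates are compared and part of their spread may be real. Here there is one centre and there are no studies, only a few strata of the same 68 patients. A label such as substantial or considerable would then sound like a measured degree of effect modification when it only restates a P value on another scale.

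The flag also has a consequence. If it often arises by chance, chance decides when the data are reanalysed in ways not fixed beforehand. In an unblinded trial where allocation depends on owning a compatible phone, that would weaken confidence in the reported effects.

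**Working it through.** **Inputs.** From the article: test level 0.10; I-squared bands 50% and 75%; 28 patients per group, 34 after the loss allowance, 68 in total; expected response 80% against 40%. Assumed: three variables (age, gender and socioeconomic status, which the article names for the propensity score under Study Population and Sample); two to four strata per variable; independent checks.

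**The plan's own sample size.** For 80% against 40%, two-sided 5% and 80% power, the two-proportion formula gives 23 per group, or 28 with continuity correction. Then 28 × 1.2 = 33.6, rounded up to 34, and 2 × 34 = 68. The stated size reproduces and is not affected by this point.

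**What the bands mean.** With k strata and no effect modification, Q follows a chi-square distribution on df = k − 1. Since I² = 1 − df/Q, I² > 50% is the same as Q > 2·df, and I² > 75% is the same as Q > 4·df.

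| Strata | Chance of I² > 50% | Chance of I² > 75% | Q at P = .10 | I² at P = .10 |
|---|---|---|---|---|
| 2 | 15.7% | 4.6% | 2.706 | 63% |
| 3 | 13.5% | 1.8% | 4.605 | 57% |
| 4 | 11.2% | 0.7% | 6.251 | 52% |

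Each band is therefore a P-value cut-off that shifts with the number of strata: the 75% band is P < .046 with two strata and P < .008 with four. With two to four strata, any result with P<.10 already has I² above 50%, so the lower band adds nothing once the test is passed.

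**False flags per check.** In theory 10%. In simulation (40,000 runs, 28 or 34 per arm split into strata, no effect modification) the rate was 10–11% with two strata, 12–13% with three and 13–15% with four.

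**False flags over several checks.** The chance of at least one at P<.10 is 1 − 0.9^m:

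- three variables, one primary outcome, m = 3: 1 − 0.9³ = 27%
- three variables, four outcomes (blood pressure, adherence, physical activity, diet), m = 12: 72%
- three variables, five outcomes (systolic and diastolic separate), m = 15: 79%

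**Real effect modification.** Take two equal strata with intervention response 90% and 70%, and control response 40% in both. With 17 per arm per stratum, the variance of the difference between the two effects is (0.09 + 0.24 + 0.21 + 0.24)/17 = 0.0459. The noncentrality is 0.20²/0.0459 = 0.87, and power at P<.10 is about 24%. With 14 per arm per stratum it is 22%.

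**The case against.** - **The test does address effect modification.** With two strata, Q on the stratum-specific effects is the squared z statistic for their difference, which is an interaction-type test. This stands. A reader might infer that the plan cannot answer the question at all, and that goes too far. The faults are the I-squared layer, the lack of a stated effect estimate to feed Q, and the open consequence.
- **The two criteria need not conflict.** The text gives the Chi-square test the role of judging chance and I-squared the role of describing size. On that reading I-squared is not a trigger. A reader might instead take I² > 50% as the trigger and compute, for 15 checks with two strata, 1 − (1 − 0.157)^15 = 92%. The article does not state that trigger, so the figure is not supported.
- **The number of checks is not in the article.** This also stands. The three variables are borrowed from the propensity score sentence, and the count of outcomes is a reading of the list. Outcomes are correlated, systolic and diastolic pressure plainly so. Calling false heterogeneity almost certain is not supported.
- **The consequence is a sensitivity analysis.** A reader might infer that a flag replaces the primary result. The article does not say so. Its general permission to modify techniques is a separate sentence, tied to the nature of the data and not to a heterogeneity flag. What remains is that the alternatives are unnamed and their use depends on the flag.
- **Detail may sit elsewhere.** Subgroup lists and named sensitivity analyses can properly be left to a fuller document. The point rests on what the article does fix: the statistic, its bands, and the dependence of further analysis on a flag.

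**Conclusion.** The point holds in a limited form. I-squared and its 50% and 75% bands do not suit strata of a single-centre trial of 68 patients: they add nothing to Q, and with two strata and no effect modification they are exceeded in 15.7% and 4.6% of checks. These rates rest only on the chi-square reference distribution. The planned test flags about 10% of checks by chance, somewhat more with three or four strata. Across checks, at least one false flag has a chance of 27% (three variables, one primary outcome) to about 79% (five outcomes). That range assumes three variables and independence, and is an upper guide. Power for a real 20-point difference in response is only about 22–24%, so a flag, or its absence, says little. The consequence is a sensitivity analysis of undefined form, not replacement of the primary analysis. The paragraph should be changed.

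**What to change.** 1. Delete the I-squared statistic and both cut-offs.
2. State a between-group model of post-intervention blood pressure adjusted for baseline. Add group-by-age, group-by-gender and group-by-socioeconomic-status terms to it, one at a time.
3. Report each interaction estimate with its 95% CI, labelled exploratory.
4. Name any sensitivity analyses in advance and run them whatever the heterogeneity result, with no trigger to change the primary analysis.

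**Cost.** No extra data and no change in sample size, but more than one paragraph of rewriting, because the between-group model has to be written first. The estimates will be imprecise: with two equal strata and equal variances, the difference between two stratum effects has four times the variance of the overall effect, hence twice its standard error. Nor does the change abolish chance findings. Three interaction terms each read at 0.05 still give 1 − 0.95³ = 14% for at least one under independence. That is why they should be read as estimates and trigger nothing.

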### Nonrandomized Controlled Trial

This is an applied research of technological innovation with software development and analysis of its effects through a controlled, nonrandomized, nonblind, prospective, and monocentric clinical trial. The Research Ethics Committee of the University of Passo Fundo, Rio Grande do Sul, Brazil (report 3.414.793) approved this project, which was registered in the Brazilian Platform of Clinical Trials under the code RBR-2rkkgn (Universal Trial Number U1111-1230-7550). Figure 2 presents the trial design and flowchart.

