#### Study Population and Sample

The study population will include men and women under treatment for arterial hypertension who will be assisted by health professionals in the public health system of a Brazilian city. After the invitation to take part in the study, the participants will sign a consent form. The effect (primary outcome) is expected to be 80% in the intervention group and 40% in the control group, which means a 40% difference. These proportions are based on the findings of the study by Neumann et al [22], which was conducted with a similar design, and also on more optimistic results obtained from one of our pilots [19]. For sample calculation, we used Epi Info version 6.0 software (Centers for Disease Control and Prevention, Atlanta, Georgia; sample size/2 proportions). We considered an estimate of 40% proportion difference between groups, 95% confidence interval, and 80% statistical power (beta). The calculation resulted in 28 individuals for each group, but to minimize the effects of loss and refusal during the intervention, we added 20% to the size, yielding a total of 34 individuals in each group.

The allocation of patients in each group will be based on the eligibility criteria. For example, if the patient fits all the criteria but does not have a mobile phone compatible with the app, then he or she will be allocated to the control group. If the patient has a mobile phone compatible with the app, he or she will be allocated to the intervention group. For propensity score calculation, based on the effect of confounding factors or predictors of exposure (to intervention), we will consider demographic variables of age, gender, and socioeconomic status.

We will consider the following inclusion criteria:

Cognitive ability confirmed by the Mini-Mental State Examination [23] (both groups)Current medical monitoring for the treatment of hypertension in the public health system of the city of Passo Fundo, RS, Brazil (both groups)Possibility to measure blood pressure in drugstores, hospitals, Family Health Strategies, or centers for comprehensive health care (both groups)Possession of an Android mobile phone, version 4.3 or higher (intervention group)Familiarity with the use of apps (intervention group)Internet access on the smartphone (intervention group).

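### An open permission to change every analysis in the light of the data, in a nonblind trial with two named blood pressure tests and two pressures, leaves the 5% level unguaranteed for the primary conclusion

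*Protocol article*

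**What the plan says.** All references are to the protocol article.

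- **Permission to change.** Near its end, the Statistical and Qualitative Analysis section says: "All analysis techniques can be adjusted or modified, if required, by the characteristics of the collected data". No analysis is exempt. No condition beyond need is given, and nothing says when the decision is taken or whether group results are hidden at that point.
- **Design.** Under Nonrandomized Controlled Trial the study is a "controlled, nonrandomized, nonblind, prospective, and monocentric clinical trial".
- **Primary outcome.** It is described as blood pressure coming down and stabilising. Neither systolic nor diastolic pressure is chosen.
- **Blood pressure tests.** The section first assigns blood pressure data to the paired t test. After naming the Mann-Whitney test for the adherence score it adds: "The same test may be used to compare diastolic and systolic blood pressure measurements", before and after the intervention.
- **Normality.** A Kolmogorov-Smirnov check is planned. The parametric-or-Wilcoxon alternative is offered for quantitative variables other than blood pressure.
- **Error level.** "We will consider a 95% confidence interval (*P*<.05").
- **Sample size.** Under Study Population and Sample: "The effect (primary outcome) is expected to be 80% in the intervention group and 40% in the control group", with "95% confidence interval, and 80% statistical power (beta") and "The calculation resulted in 28 individuals for each group", raised by 20% to 34. The same section plans a propensity score from age, gender and socioeconomic status.

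**The concern.** A 5% test keeps its error rate only if the test and the variable are settled without regard to how the group comparison came out. Here the text allows the method to follow the data, and an open design does not by itself keep those choosing the method from knowing the group results.

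The permission also lands on a primary analysis that is not yet single. The paired t test asks whether pressure changed within a group. The Mann-Whitney test, read as a between-group comparison, asks whether the groups differ. Each can be applied to either pressure. A reader of the final report could not tell a planned primary result from one picked among several. In a trial of 68 participants allocated by phone ownership, that weakens the main conclusion.

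**Working it through.** **1. The plan's own figure.** Inputs: p1 = 0.80, p2 = 0.40, mean 0.60, two-sided alpha 0.05 (z = 1.960), power 0.80 (z = 0.842).

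- Uncorrected: n0 = [1.960 × √(2 × 0.6 × 0.4) + 0.842 × √(0.16 + 0.24)]² / 0.40² = (1.358 + 0.532)² / 0.16 = 22.3.
- Continuity-corrected: n = (n0/4) × [1 + √(1 + 4/(n0 × 0.40))]² = (22.33/4) × (1 + 1.203)² = 27.1, rounded up to **28**, as stated.
- 28 × 1.2 = 33.6, rounded up to **34**, as stated.

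So the design was sized for one two-sided 5% test. The question is whether the analysis text holds to one such test.

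**2. Upper reference.** With k independent looks at 5%, the chance of at least one P<.05 is 1 − 0.95^k: 9.8% for k = 2 and 18.5% for k = 4. The tests here are correlated, so the true figure is lower.

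**3. Simulation with no effect.** These inputs are assumptions, not in the document:

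- normal data, systolic-diastolic correlation 0.6, pre-post correlation 0.5 or 0.6;
- paired t test taken within the app group;
- Mann-Whitney test taken between groups on post-intervention values.

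There were 20,000 null trials per setting. The Monte Carlo standard error is about 0.15 points near 5% and 0.26 points near 16%. Entries are the percentage of trials with the smallest P below .05.

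| n per group | Pre-post r | Mann-Whitney, systolic only | t or Mann-Whitney, systolic | Paired t or Wilcoxon, systolic | Paired t, either pressure | Mann-Whitney, either pressure | Any of the four named |
|---|---|---|---|---|---|---|---|
| 28 | 0.5 | 5.1 | 6.2 | 6.0 | 9.1 | 8.8 | 16.7 |
| 28 | 0.6 | 4.9 | 5.9 | 6.0 | 9.2 | 8.6 | 16.6 |
| 34 | 0.5 | 4.6 | 5.6 | 5.8 | 8.8 | 8.3 | 15.9 |
| 34 | 0.6 | 4.6 | 5.7 | 6.0 | 8.9 | 8.3 | 16.0 |

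Widening both correlations to 0.5 to 0.7 gives 15.1 to 16.7% in the last column. If a normality test, rather than the smaller P value, decides between paired t and Wilcoxon on systolic pressure, the rate is about 5.3 to 5.6%.

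**4. Reading the table.**

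- One pre-specified between-group test on one pressure stays at about 5%.
- Switching between a parametric and a rank test on one pressure adds at most about one point.
- Leaving the pressure open, even with the paired t test alone, gives about 9%.
- Leaving both pressure and test open gives about 16 to 17%.

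Most of the rise comes from the unselected variable and the unselected comparison. The quoted sentence adds to this because nothing in the text then closes the choice.

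**The case against.** **The sentence may mean distributional checks only.** It is conditional on need and refers to characteristics of the data, normality testing is planned, and it directly follows remarks on sensitivity analysis. On that reading the inflation is about 5 to 6%, which is minor. The reading is plausible, but the wording covers all techniques and does not limit itself to failed assumptions.

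**The larger figure does not isolate the sentence.** This stands. All four tests behind it are already named, so deleting the sentence alone would leave 16 to 17% unchanged. The figure also pools two hypotheses and is not the error rate of a single primary comparison. Nor does the article say that the smallest P value will be reported.

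**A condensed article leaves detail to an analysis plan.** True, and when methods are finalised may be settled there. But the point rests on a permission the article states, not on something it omits.

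**Stronger readings that the document does not support.**

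- A reader might infer that the 5% level is void. The text shows only that it is unprotected. Nonblind does not establish that methods will be chosen after group results are seen.
- A reader might add change-score or responder tests of blood pressure and obtain a larger inflation. The analysis section names no such tests for blood pressure.
- A reader might count the regression ("If feasible, we also intend to analyze the results with logistic regression of preintervention and postintervention data") as another route to the primary result. Its dependent variable is app use, and its named predictors are sociodemographic variables and secondary outcomes. It is not evidence here.

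**Conclusion.** The concern holds in this form: the article permits data-dependent change to every analysis, the primary one included, without trigger or timing, while the blood pressure analysis leaves both the test and the pressure open. P<.05 is therefore not guaranteed for the primary conclusion.

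The size depends on how much of the freedom is used: from little more than nominal for a distributional switch on one pressure to roughly three times nominal if any named result may be taken as primary. These bounds rest on normality, the assumed correlations, and the readings of the two tests given above. The document supplies none of these. The point deserves correction because it touches the main conclusion and the remedy is nearly free. It is not evidence that any result will be selected.

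**What to change.** Replace the sentence with a rule along these lines:

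*The primary analysis is one between-group comparison of post-intervention systolic [or diastolic: name one] blood pressure, adjusted for its baseline value and for the propensity score described under Study Population and Sample. It is fixed before post-intervention data are examined by group. If its assumptions fail, a bootstrap or rank-based version of the same comparison is reported beside it. The paired t test, the other pressure and any other change of method are labelled secondary or exploratory.*

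The trial team must choose the pressure and state it. The propensity score belongs in the rule because allocation follows phone ownership and the plan already provides for the score.

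**Cost.** Protocol or analysis plan wording only, with no change to visits or data collection. The downside is less freedom to change methods later, eased by the named fallback. The 28 per group was derived for two proportions, so its 80% power does not carry over automatically to a comparison of means. By the normal approximation, 28 per group detects (1.960 + 0.842) × √(2/28) = 0.75 SD. Baseline adjustment at an assumed correlation of 0.5 to 0.6 multiplies this by √(1 − r²), giving 0.65 to 0.60 SD, before any loss of precision from the propensity score. The team should state this beside the chosen analysis.

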Previous studies have shown positive results in the improvement of blood pressure from simple lifestyle changes supported by eHealth solutions [9]. The results by Toro-Ramos et al [10] indicated a decrease in diastolic pressure and body weight of the 73 participants. In the study by Ashoorkhani et al [11], tests for 132 patients with hypertension showed an improvement in treatment adherence, weight control, and regular blood pressure verification. The study by Albini et al [12] with 690 hypertensive patients suggests that information and communication technology tools may be effective in providing physicians with dynamic patient control and in improving the monitoring of hypertension and adherence to treatment prescriptions.

In the studies mentioned above [10-12], periodic verification was essential for obtaining favorable results. However, a prominent challenge in the market of mobile apps is maintaining long-term or recurrent use of the app among users engaged with the app, without loss of interest. Among the leading causes of abandonment from the users of these apps are quitting after achieving goals and the lack of resources available [13]. Several techniques have been used to allow greater user engagement with the app, such as gamification, which comprises applying gaming elements to a nongaming context [14].

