### Prior Work

We have devised a platform for monitoring the health conditions of patients with arterial hypertension. We implemented an initial version, considered a prototype, and made it available to use for initial validations. The platform includes a server that centralizes the data for a website interface [15] that is designed for health professionals, and a mobile app with gamification elements [16] that is designed for patients.

We performed pilot studies with health professionals and patients to assess the prototype functionalities [15] and patient engagement and experience with the app [16-18], respectively. The assessment with health professionals showed some benefits of using the system, such as the optimal visualization of patients’ logbooks. Patient assessments showed that gamification favors engagement with health treatment. We also found that participants under follow-up with a health professional interacted more with the app and were more motivated to maintain their health monitoring. Therefore, the use of digital health resources by professionals, along with patients, may promote a higher commitment to monitoring the treatment factors [17]. To verify the clinical effects, we have already conducted a pilot trial [19], including 39 patients with arterial hypertension, to compare the use of the platform’s initial version with conventional hypertension monitoring over a period of 3 months. The patients who used the mobile health app had a change in systolic and diastolic pressure toward more adequate levels. In addition, the group had improved levels of glucose and high-density lipoprotein cholesterol and a reduced consumption of ultraprocessed foods.

The main goal of our project is to assess the effects of using the eHealth platform—which will be developed—on health conditions of patients with hypertension, with assistance from health professionals in the public health system.

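### The optional logistic regression models app use on the secondary outcomes, so with several outcomes entered together it does not give the platform's adjusted effect on any of them

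*Protocol article*

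**What the plan says.** All places are in the Protocol article.

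- **Aim (Prior Work).** The project is to "assess the effects of using the eHealth platform" on the health conditions of patients with hypertension. Platform use is the exposure and health is the outcome.
- **Allocation (Study Population and Sample).** "If the patient has a mobile phone compatible with the app, he or she will be allocated to the intervention group". Patients without such a phone become controls. The same section announces a propensity score from age, gender and socioeconomic status.
- **Logistic regression (Statistical and Qualitative Analysis).** It is conditional: "If feasible, we also intend to analyze the results with logistic regression of preintervention and postintervention data". The roles follow: "In this case, the dependent variable will consider the base category" of whether the user used the app. The independent variables are "variables of interest such as sociodemographic variables and the expected secondary outcomes".
- **Chi-square test (same section).** For adherence, physical activity and diet, "we will apply the Chi-square test while considering the app use as the dependent variable", and "the independent variables will be treatment adherence, physical activity, and dietary intake".
- **Other tests (same section).** Blood pressure has a paired t test and possibly a Mann-Whitney test. The adherence (MBG) score has a between-group Mann-Whitney test.

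**The concern.** Group membership is settled before any post-intervention outcome exists, so later outcomes cannot explain it. A model of app use on sociodemographic variables and outcomes resembles a propensity model with post-treatment variables added. Each coefficient says how strongly one outcome is associated with app use given the other outcomes. The trial asks something else: by how much the platform changes each outcome, given the patient's background.

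This matters more here than in a randomized trial. Owning a compatible phone, being familiar with apps and having internet access may well go with age and socioeconomic status, so an unadjusted comparison is hard to interpret. In the analysis section this regression is the only between-group outcome analysis described with covariates. The Chi-square and Mann-Whitney tests are unadjusted, and the section attaches the propensity score to none of its tests. The heterogeneity check considers demographic variables but is not described as an adjusted group comparison.

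**Working it through.** **1. The plan's own figure.** Inputs from Study Population and Sample: 80% and 40%, 95% confidence, 80% power (two-sided assumed).

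- Without continuity correction: n = [1.96 × √(2 × 0.6 × 0.4) + 0.8416 × √(0.8 × 0.2 + 0.4 × 0.6)]² / 0.4² = (1.358 + 0.532)² / 0.16 = 22.3, so 23.
- With continuity correction: (22.3 / 4) × [1 + √(1 + 4 / (22.3 × 0.4))]² = 27.1, so 28, as stated.
- Adding 20%: 28 × 1.2 = 33.6, so 34, as stated.

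The sample size reproduces, and the direction of the model does not affect it.

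**2. Chi-square.** Illustrative table close to 80% and 40%: 27 of 34 against 14 of 34.

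- Statistic: 68 × (27 × 20 − 7 × 14)² / (34 × 34 × 41 × 27) = 10.38, P = 0.0013 (with continuity correction 8.85, P = 0.0029).
- Exchanging rows and columns leaves the formula unchanged, so both values are the same whichever variable is called dependent.
- Odds ratio: (27 × 20) / (7 × 14) = 5.51, and a logistic model with one predictor gives 5.51 in either direction.

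**3. Why several outcomes together differ.** By Bayes' rule, the log odds of being an app user given the outcomes equal a constant plus the log of P(outcomes | user) / P(outcomes | control). If the outcomes are independent within group, this ratio factorises and each coefficient is that outcome's own log odds ratio. If they are correlated, they carry overlapping information, and each coefficient shows only what that outcome adds to the others.

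**4. Size, by simulation.** Three binary outcomes and 200,000 patients per group. Each outcome comes from a latent normal variable, √ρ × shared part + √(1 − ρ) × own part, cut to give the required rate. The rates 80% and 40% are borrowed from the primary-outcome assumption; the true odds ratio is (0.8/0.2) / (0.4/0.6) = 6.0. The document gives no correlations, so ρ is an assumption shown over a range.

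| ρ (assumed) | Outcome on group, each outcome | App use on three affected outcomes | App use on two affected and one unaffected outcome: odds ratio of the unaffected one (true 1.0) |
|---|---|---|---|
| 0 | about 6.0 | about 6.0 | 1.00 |
| 0.3 | about 6.0 | about 3.65 | 0.56 |
| 0.5 | about 6.0 | 2.92 to 2.98 | 0.38 |
| 0.7 | about 6.0 | 2.44 to 2.48 | 0.24 |

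Models with the outcome as dependent variable recover 6.0 (or 1.0) at every correlation. The reversed joint model shrinks real effects and can make an unaffected outcome look harmed.

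**The case against.** The strongest reply is that direction alone does no harm. This is largely right. The Chi-square result is unchanged, and a reversed logistic model with a single outcome gives the same odds ratio without covariates and essentially the same with them: a simulation with three covariates and assumed coefficients gave 2.71 in both directions. The distortion needs several correlated outcomes in one model. The text names sociodemographic variables and the secondary outcomes together as independent variables of one regression. Joint entry is therefore the natural reading, but it is not spelled out.

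It is also fair that the regression is offered only if feasible, that the section allows techniques to be adapted, and that adherence has a between-group Mann-Whitney test which the reversal does not touch. These points lower the severity but do not make the model, run as written, answer the trial's question.

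A reader might infer more in three ways, none of which the document supports:

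- **That the Chi-square analysis is invalid.** Only its labels are wrong. It gives no effect size and no adjustment in either direction, but the reversal does not cause that.
- **That the primary outcome is compromised.** Blood pressure is named in neither analysis and has its own tests.
- **That patients who abandon the app would be counted as controls.** The Background does say that "a prominent challenge in the market of mobile apps is maintaining long-term or recurrent use of the app among users", but this concerns the app market in general. The Intervention Period section defines the groups as app users and users of paper logbooks, and log-based use is a separate measure. No passage moves patients between groups. The wording of the dependent variable leaves actual use open as a reading, which justifies a clearer definition but no estimate of bias.

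**Conclusion.** The concern holds for the optional logistic regression. As specified, with several secondary outcomes entered together, it does not yield the platform's adjusted effect on any of them. For ρ between 0.3 and 0.7, a true odds ratio of 6.0 becomes about 3.7 to 2.5, and a true 1.0 becomes about 0.56 to 0.24. These sizes rest on assumed correlations, borrowed rates and joint entry; at zero correlation, or with one outcome per model, they vanish. Some correlation among adherence, diet and activity within a patient is plausible, but the document gives no value.

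The Chi-square wording is a labelling error without numerical consequence. The point is worth correcting before analysis because this regression is where the section brings covariates into a nonrandomized comparison. It is not a must-fix.

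**What to change.** 1. Replace the regression with one model per secondary outcome: adherence, adequate diet and adequate activity. Make the outcome the dependent variable and group the exposure, with age, gender and socioeconomic status as covariates, or the propensity score already announced.
2. Add the baseline value only where it is collected. The Preintervention Period section lists only the characterisation and MBG questionnaires, so this applies to adherence. The SISVAN questionnaire, which defines adequate diet and activity, is not listed there.
3. Define the exposure as allocated group, and report log-based app use descriptively.
4. In the Chi-square sentence, exchange the labels so that group is the independent variable and each outcome the dependent one. The test itself stays as it is.

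The cost is a change of analysis wording. Sample size, visits and data collection stay as planned.
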